## Abstract

**Background:**

There is current controversy about the efficacy of smoking cessation interventions that are based on information obtained by spirometry. The objective of this study is to evaluate the effectiveness in the primary care setting of structured motivational intervention to achieve smoking cessation, compared with usual clinical practice.

**Methods:**

**Discussion:**

Application of a motivational intervention based on structured information about spirometry results, improved abstinence rates among smokers seen in actual clinical practice conditions in primary care.

**Trial registration:**

ClinicalTrial.gov, number NCT01194596.

## Background

Smoking is the principal avoidable risk factor and etiological cause of numerous pathologies, including respiratory tract [1]. Smoking accelerates the physiological decline of pulmonary volume usually attributable to age, and the most susceptible subjects may develop chronic obstructive pulmonary disease (COPD) [2]. The estimated absolute risk of COPD for smokers is at least 25% [3]. The prevalence of COPD increases with age and is more frequent in men, but this appears to be related to the cumulative effect of other risk factors to which the individual has been exposed during a lifetime [4]. Spirometry is considered the standard test for the diagnosis and monitoring of COPD [5,6]; nevertheless, it appears to be an inefficient screening tool for the general population. Some institutions advise against its systematic use in asymptomatic subjects for various reasons, not only cost-benefit considerations [7]. In addition, the available evidence seems to indicate that the information spirometry provides does not modify COPD management in the early stages of disease [8], when quitting a smoking habit is the most effective therapeutic intervention and the only one that increases survival [1]. Therefore, early intervention is considered crucial.

From a therapeutic perspective, smoking is a chronic disease of an addictive nature, with frequent relapses that reflect the intensity of nicotine dependence. The available data suggest that most smokers are interested in quitting and that structured advice from health professionals with whom they are in contact is an important motivating element [9]. Therefore, interventions based on individual or group counselling should be the first step in smoking cessation, with the addition of pharmacological treatment when educational strategies have not been effective [10]. In fact, the combination of advice and medication is more likely to succeed than either approach in isolation. In patients with COPD, a recent study indicates that rates of abstinence increase as interventions are added, from 2.6% with brief counselling to 12.3% when combined with drug therapy [11]. However, while it is true that adding medication significantly improves abstinence, cessation efforts often fail because of the lack of motivation of smokers [12]. In an effort to improve success rates, spirometry was advised as a motivational tool to reinforce the smoking cessation message provided by counselling [13].

Some years ago, the Lung Health Study showed that COPD could be detected early through the use of spirometry and established the benefits of smoking cessation for changing the natural history of the disease [14]. In addition, the quit rate among participants included in the intensive program was 21.7%, compared to 5.4% among subjects in the standard program [15,16]. Bednarek et al. [17] have also published results obtained in a cohort of 4494 smokers in Poland who received a minimal intervention, placing their spirometry data on the classic Fletcher-Peto graph [18]. After 1 year of follow-up, the cessation rate was significantly higher in patients with COPD than in subjects with normal spirometry (16.3% vs 12.0%; *P *= 0.0003). Therefore, it is logical to assume that information about respiratory function testing could also be helpful. However, these results are from observational studies lacking sufficient statistical power to support any recommendations, leading some authors to find the evidence of the motivational merits of spirometry testing to be less than convincing [19,20].

At present, the use of spirometry as a motivational tool for smoking cessation continues to be a controversial topic. The most recent Cochrane review of the assessment of biomedical risks as a quit-smoking aid insists that, due to the scarcity of high-quality analyses, no definitive conclusions can be reached about the effectiveness of this approach [21]. However, it also points out that spirometry had a significant effect in the only high-quality study, published in 2008 by Parkes et al. [22]. This clinical trial included 561 smokers older than 35 years who, after spirometry testing, were randomized to study groups, one of which received a summary of the results, describing their "lung age" and comparing it with their chronological age. After 12 months follow-up, abstinence rates confirmed by urinary cotinine levels were significantly higher in the intervention group (13.6% vs 6.4%, *P *= 0.005) and these subjects had a higher probability of abandoning their habit than those who did not receive this explanation (RR: 2.12; IC95%: 1.24-3.62). Moreover, Kotz et al. published a clinical trial in 2009 with the hypothesis that early detection of COPD and the provision of information about the results could be more effective than standard efforts to help smokers to quit [23]. The study evaluated 296 smokers aged 35-70 years with COPD detected by spirometry testing, who were randomly assigned to either confrontational counselling for smoking cessation in which a nurse respiratory specialist provided feedback on the results (experimental group) or "care as usual" for smoking cessation delivered by the general practitioner. After 52 weeks of follow-up, the intervention group achieved higher abstinence rates (11.2% vs 5.9%), although without reaching statistical significance (OR: 2.02; IC95%: 0.63-6.46). These studies appear to present contradictory results, although congruence emerges if we analyze them in detail: the use of spirometry in "healthy" smokers increases motivation (and the probability of quitting smoking), while confrontation with their lung function data is less effective in subjects with COPD. More recently, in 2010, McClure et al. [24] published a clinical trial with 536 smokers, recruited from the general North American population, who were randomized to receive a brief motivational intervention for smoking cessation (≈20 min), including spirometric testing and feedback; no differences in abstinence rates were found at 1 year of follow-up. However, in a later publication they reported that the participants with changes in their lung function tests made greater use of quit-smoking services and achieved an abstinence rate almost double that of controls at 6 months (17.2% vs 8.9%, *P *= 0.05; OR: 2.13, IC95%: 1.04-4.5), although the effect was diluted at 12 months (16.2 vs 11.3, *P *= 0.26; OR: 1.52, IC95%: 0.73-3.1) [25]. Therefore, given these other results, they concluded that more research is NEEDED to determine whether the impact of spirometry feedback differs according to the deterioration in the smoker's pulmonary function.

## Objectives

The main objective of this study is to evaluate the effectiveness in the primary care setting of a structured motivational intervention and feedback on spirometry data to achieve smoking cessation, compared with usual clinical practice and assessed with respect to quit rates at 12 months after the intervention.

## Methods

### Design

A randomized, controlled clinical trial is proposed, enrolling current smokers with no previous history of respiratory disease in the Primary Care Centres of the province of Tarragona (Spain). The general design of the study is detailed in Figure 1. This trial has been registered with ClinicalTrial.gov (NCT01194596).

**Figure 1 F1:**
[figure not shown]
**Diagram of the ESPITAP study: process of selection, randomization and follow-up of subjects included in the study**.

### Setting and study sample

The study population will be recruited during consultations in 12 primary care practices in the province of Tarragona (Spain) managed by the Catalan Health Institute, 8 of which are urban and 4 rural, serving an adult population (aged > 18 years) of 195, 343 patients. Candidates for participation are smokers aged 35 to 70 years who visit a centre for any reason during regular office hours, and who meet all inclusion criteria and none of the exclusion criteria.

- *Inclusion criteria*: current smoker, with a cumulative consumption of more than 10 packs/year.

Current smoker is defined as having smoked daily during the past month, regardless of the quantity. Cumulative consumption is defined as the daily average of cigarettes smoked, multiplied by the number of years of smoking, divided by 20.

- *Exclusion criteria*:

1) Any evidence of previous diagnosis of a respiratory disease,

2) Functional pulmonary testing conducted within the previous 12 months,

3) Presence of any chronic or terminal condition that changes the baseline parameters or complicates the testing and analysis to be conducted during the study period,

4) Impossibility of completing follow-up for any reason,

5) Patient refusal to continue with the study.

### Measurements

In the recruitment visit (visit 0), all potential subjects will be advised that smokers are susceptible to COPD and that spirometry is a simple, non-invasive test that permits the detection of this disease at an early stage. They will then be informed about the study and offered the possibility of participating. Those who accept will be asked to provide their signed informed consent. Consenting participants will then be asked for all of the necessary information using a structured data collection questionnaire designed for this purpose, which will include:

• Affiliations and sociodemographic data.

• History of diseases and medications.

• History of respiratory symptoms.

• Smoking habit: current daily consumption (cigarettes/day) and accumulated consumption (packs/year averaged over years of smoking), nicotine dependence measured by the Fagerström test [26], motivation to quit smoking using the Richmond test [27] and stage of the change process according to Prochaska and DiClemente's model [28].

• Previous quit attempts: number and therapeutic resources used.

• Basic physical examination: weight, height, body mass index, blood pressure.

• Expired carbon monoxide (CO) levels determined by coximetry using the Smoke Check device (Micro Medical Limited, Rochester, Kent, England). This model detects a CO range of 0-20 particles per million (ppm) with a sensitivity of 1 ppm.

• Spirometry and a bronchodilator test, using an ultrasound pneumotacograph Datospir-600 (SIBELMED, S.A.).

### Allocation of study groups

All patients will be scheduled for assessment of their lung function, using spirometry, at their primary care centre. The quality of testing will be ensured by a three-tiered system of quality control:

1) Standardization of pulmonary function testing. Only tests that meet the quality recommendations and criteria of the *American Thoracic Society-European Respiratory Society *[29,30] will be accepted as valid:

a) At least three attempts will be made, with the selection of the best values of forced vital capacity (FVC), forced expiratory volume in 1 s (FEV1), and FEV1/FVC ratio;

b) Variability between these measures must be less than 5%, exhalation time greater than 6 s, and the attempt must be properly initiated, with a rapid increase;

c) Airflow-limitation reversibility will be determined and considered positive if it is greater than 12% and improvement in FEV1 > 200 ml, observed after the administration of 400 micrograms of salbutamol inhaled with a valve-holding chamber (spacer).

2) Technical considerations. To facilitate access, all testing will be conducted at each participating centre by technicians selected from the nursing staff, who must be able to show specifically accredited training from the Health Research Institute of Catalonia.

3) Centralized supervision. All testing will be sent to one reference observer who will be responsible for centralized quality control and will interpret the results by following an automated process using a previously validated and registered computer program (ESPIRO) [31]. Finally, a clinical report will be generated and analyses will be considered normal if they meet the following criteria:

- FEV1 ≥ 80% of the theoretical reference value

- FVC ≥ 80% of the theoretical reference value

- FEV1/FVC ≥ 0.7

Subjects with test results within normal range will be allocated to receive or not the proposed intervention. The assignment sequence will be centralized at the Research Support Unit of the IDIAP Jordi Gol in Tarragona and will be blinded and performed consecutively, following a simple, numerical relationship randomization issued for this purpose. Due to the nature of the intervention it is impossible for the patient or the researcher to be blinded to the assignment.

#### Description of the intervention and control group

Within one month of their random assignment, all participants will be contacted to schedule their intervention visit (visit 1), during which they will receive health education and counselling on smoking cessation from their physician (Table 1). Control group subjects will have a brief visit (5-10 min) in the format that is usually recommended for primary care professionals [32]: a clear, firm, personalized proposition recommending that they quit smoking, in an empathic and respectful context.

**Table 1 T1:** Smoking cessation counseling protocol

Smoking cessation counseling protocol
Control group counseling: brief intervention

*"As your doctor, I recommend that you quit smoking, although the decision is yours alone. I know that it is difficult to make a decision right now, but we have a number of resources that can help you quit smoking and I know that if you decide to quit in the future you will be able to do that. Remember that you can always count on us to help."*

Intervention group counseling: detailed discussion of spirometry

*"Tobacco is harmful to your health. Smoking can produce various diseases such as, for example, those that affect your lungs. Some smokers end up getting a chronic pulmonary disease that is commonly called chronic bronchitis. To diagnose that disease, we use a test called spirometry that measures lung capacity. This is the test I gave you. In your case, the results indicate that you do not have this disease now, but some of the data suggest that tobacco is causing some changes in your lungs*.

*These values - FVC, FEV_1_, FEV_25-75 _- indicate that you have lost part of the capacity you had to exhale air, specifically, you have lost about..........%*.

*Tobacco also accelerates the usual aging of the lungs. This effect can be seen in this "lung age" value, which is....... years*.

*In summary, although at this time, given your results, we would not say you are sick, looking at the rest of the data, the best thing for your health is to stop smoking as soon as possible."*

Patients assigned to the intervention group will receive a written spirometry report and a detailed, structured explanation of the content during a personalized visit of 15 to 20 min, using a motivational interview approach. Researchers at the participating centres will come to a consensus on the comments about spirometry to be delivered, and these will focus on a standardized description of FEV1, FVC, forced expiratory flow between 25% and 75% of the FVC (FEF25-75%) and peak expiratory flow (PEF) values and their interpretation in terms of their theoretical value. In addition, they will inform subjects about the lung age index (defined as the average age of a non-smoker with the same FEV1 value as the subject in question) [33], comparing this value with the chronological individual age to illustrate the lung damage suffered as a consequence of smoking. In practice, the lung age is automatically generated by configuring the spirometer. The Fletcher-Peto graph [18] will be used to depict how the loss of lung function that occurs with age can be accelerated in smokers and how quitting smoking normalizes the pace of pulmonary deterioration, even though the lost capacity cannot be recovered.

With respect to patients with changes in their test values (FEV1 and/or FVC < 80% of the theoretical value and/or FEV1/FVC < 0.7), all will be informed about them and also referred to their physician for evaluation, verification of test results, and clinical follow-up according to the standard practice at each centre.

Independent of their group assignment, all participants who show an interest in quitting smoking will be offered a treatment option in the smoking cessation program that forms part of the usual activities of each centre.

Both physicians and nurses at the participating centres will receive support and at least 8 h of specific training on spirometry and motivational interview techniques, applied to smoking addiction, which will be accredited by the Catalan Health Institute.

#### Follow-up period

All subjects will be evaluated during a telephone follow-up at 6 months post-intervention (visit 2) to determine whether there has been any change in their smoking status and to record new data about tobacco consumption or, where applicable, to record quit date. Finally, at 12 months after inclusion in the study, they will be scheduled for their final study visit (visit 3), which will take place at the corresponding centre. At this last visit, new data will be collected on each subject's smoking habit (current consumption, dependence, motivation and stage in the change process) or, where applicable, quit date. Patients who claim to have quit smoking will undergo a breath test to measure expired CO.

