#### Main outcome variables

The primary variable will be prolonged abstinence from smoking, and a secondary variable occasional abstinence (point prevalent abstinence), both of which will be validated using confirmation by coximetry at 12 months post-intervention. The cut-off point to confirm abstinence will be 10 ppm, since lower values indicate a non-smoker and higher values reflect having smoked within the preceding 12 to 24 h [34].

The criterion to establish abstinence takes into account the Society for Research on Nicotine and Tobacco recommendations and definitions [35]:

- *Continuous abstinence *refers to sustained abstinence between the point of intervention and a follow-up point.

- *Prolonged abstinence *refers to sustained abstinence from an initial "grace period" until a follow-up point. The "grace period" is understood as the time immediately after a definite quit date or intervention during which continued smoking is not considered failure to quit. For most studies, the recommendation is that this period not exceed 2 to 4 weeks.

- *Point prevalence abstinence *refers to abstinence during a time window immediately before the follow-up point (usually 7 days).

- *Failure to quit *refers to a smoking relapse (of any type) lasting 7 consecutive days (defined by the U.S. National Heart, Lung, Blood Institute).

In general, continuous abstinence is accepted as the *gold standard*, but this is a very rigorous measure; therefore, prolonged abstinence is preferred because it allows inclusion in the analysis of subjects who achieve a sustained abstinence after a transitional "grace period" and whose effort would otherwise be considered failure.

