#### Analysis strategy

Data will be drawn from a centralized database and grouped so that those responsible for analysis will be blinded to participants' study group assignment.

The effectiveness of randomization to assess the comparability and consistency of intervention and control groups will be checked in terms of the similarity of the distribution of the variables of interest at baseline. Losses to follow-up in each group will be quantified and assessed to rule out a possible selection bias.

All analysis will be conducted on the principle of intention to treat. Losses to follow-up will be quantified in each group and assessed to determine whether any possible bias was introduced to the results. A "worst-case analysis" strategy will be used, assuming that the expected response occurred in the control group patients lost to follow-up and did not occur in the intervention group. Using this assumption, the data will be reanalyzed and the magnitude of the observed difference between the initial results and the "worst-case" estimates will be assessed. This approach is valid except in the unlikely case that losses to follow-up exceed 20%.

Standard statistical tests will be used for both quantitative and qualitative variables described (e.g. means, standard deviations, medians, proportions).

Continuous abstinence, prolonged abstinence rates, and point prevalence abstinence at 6 and 12 months after intervention will be calculated, along with Cox analysis of survival (abstinence). In cases of failure to quit, consumption data, motivation, and number of attempts to quit smoking during follow-up will be collected and compared with those who achieved a level of abstinence.

The results will be presented using both relative and absolute measures: relative risk (RR) and relative risk reduction (RRR) and absolute risk reduction (ARR) and the number needed to treat (NNT), or number of smokers who must try to quit to succeed in getting one to remain abstinent. All measures will be expressed with their respective confidence intervals (CI) of 95%.

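### The final visit is timed from inclusion, but the primary outcome is defined 12 months after the intervention, so the two clocks conflict by an unstated, variable lag

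*Protocol article*

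**What the plan says.** All of the statements are in the current text of the protocol article.

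- **Follow-up period, visit 3:** "Finally, at 12 months after inclusion in the study, they will be scheduled for their final study visit (visit 3"). At that visit, "Patients who claim to have quit smoking will undergo a breath test to measure expired CO".
- **Follow-up period, visit 2:** "All subjects will be evaluated during a telephone follow-up at 6 months post-intervention (visit 2").
- **Objectives:** the comparison is "assessed with respect to quit rates at 12 months after the intervention".
- **Main outcome variables:** prolonged abstinence (primary) and point prevalence abstinence (secondary), "both of which will be validated using confirmation by coximetry at 12 months post-intervention".
- **Analysis strategy:** continuous, prolonged and "point prevalence abstinence at 6 and 12 months after intervention will be calculated".
- **Measurements:** consent and baseline data belong to visit 0 ("In the recruitment visit (visit 0), all potential subjects will be advised that smokers are susceptible to COPD").
- **Allocation of study groups:** spirometry is read centrally, and only participants with normal results are randomised.
- **Description of the intervention and control group:** the booking of visit 1 is governed by this rule: "Within one month of their random assignment, all participants will be contacted to schedule their intervention visit (visit 1"). The counselling under test is delivered at visit 1.

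**The concern.** Two time origins are in force for one endpoint. Three sections and visit 2 count from the intervention, while the visit that produces the validated endpoint counts from inclusion. The two dates are separated by at least the step from randomisation to visit 1. If inclusion means recruitment, they are also separated by spirometry and its central reading. A site that follows the visit schedule would take the breath test before the time point named in the objective, and by a different amount for each participant. A site that follows the outcome section would take it later. The published 12-month rate would then mix different lengths of follow-up.

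The time point matters for this outcome. The Background reports a spirometry-feedback trial in which, among participants with changed lung function, abstinence was 17.2% against 8.9% at 6 months (8.3 points apart) and 16.2% against 11.3% at 12 months (4.9 points apart). That subgroup differs from the participants with normal spirometry randomised here. The figures show that time points are not interchangeable; they do not estimate an error in this trial.

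**Working it through.** **1. The plan's own figure.** The Sample size calculation assumes 10% against 18%, two-sided alpha 0.05 and power 80%. With pooled variance and no continuity correction, where the mean proportion is 0.14:

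n = [1.960 × √(2 × 0.14 × 0.86) + 0.842 × √(0.10 × 0.90 + 0.18 × 0.82)]² / 0.08² ≈ 1.882 / 0.0064 ≈ 294.1, rounded up to 295 per group.

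This matches the stated 295 per group. No follow-up time enters the formula, so the sample size does not depend on this point.

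**2. Order of events.** From the sections above: visit 0 (consent, baseline) → spirometry and central reading → randomisation → contact within one month → visit 1 (intervention). The one-month limit applies to the contact. No limit is stated for the date of visit 1.

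**3. Readings of inclusion.** The word is not defined.

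| Inclusion means | Position relative to visit 1 | Effect on visit 3 |
|---|---|---|
| Recruitment (visit 0) | Before | Early by spirometry, reading, randomisation and booking time |
| Randomisation | Before | Early by booking time only |
| Visit 1 itself (loose wording) | Same | None |

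**4. Size on the first two readings.** Let L be the lag in months from inclusion to visit 1.

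- Time from intervention to visit 3 = 12 − L.
- Shortfall as a share of the planned interval = L / 12.
- Time from visit 2 to visit 3 = 12 − (L + 6) = 6 − L, against 6 months as intended.

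The article does not give L, so the values below are assumptions.

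| Assumed L (months) | Intervention to visit 3 (months) | Shortfall | Visit 2 to visit 3 (months) |
|---|---|---|---|
| 0.5 | 11.5 | 4% | 5.5 |
| 1 | 11 | 8% | 5 |
| 2 | 10 | 17% | 4 |
| 3 | 9 | 25% | 3 |

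**5. No other source for the endpoint.** Visit 2 is by telephone. No other follow-up visit with a breath test is described, so nothing else in the schedule could supply CO validation at 12 months after the intervention.

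**The case against.** The strongest reply is that inclusion may be a slip for the intervention visit, since three sections give the intended time point consistently. The design figure might settle the matter, but it is not visible in the text reviewed. This stands in part, because the early reading follows only if the visit schedule is applied as written. It does not remove the point. The same paragraph times visit 2 from the intervention, so a site could reasonably take the change of wording as a change of clock.

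A second reply is that inclusion need not mean recruitment. Only participants with normal spirometry are randomised, and the sample-size section counts the participants each centre includes by study group. On that reading the lag is only the time from randomisation to visit 1 and may be short. This stands as a limit on size: one month is a ceiling on contact and not a minimum delay, and nothing in the article supports the upper end of the range.

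A reader might infer more than the text supports on three matters:

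- **Bias between arms**, if the 15 to 20 minute intervention visit were booked later than the 5 to 10 minute control visit. The article applies one scheduling rule to all participants and says nothing about different booking times.
- **Inflated abstinence.** If prolonged abstinence is counted from a grace period after the intervention, the status can only be lost with time, so an earlier reading cannot lower the rate. The definition also allows the grace period to start from a quit date, and under that definition, as for point prevalence, a shorter interval also leaves less time to quit. The net direction is not fixed.
- **No rule for randomised participants who miss visit 1.** This is a separate detail that a condensed article may leave to the full protocol.

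**Conclusion.** The contradiction is real and concerns when the primary outcome is measured. It is a conflicting rule and cannot be put down to detail omitted from a condensed article. On either natural meaning of inclusion (recruitment or randomisation), following the schedule as written places the validated outcome 12 − L months after the intervention, with L differing between participants. For an assumed L of 0.5 to 3 months, that is 11.5 to 9 months, or 4% to 25% short of the stated interval. If inclusion was meant as visit 1, there is no shortfall, but the wording still needs correcting so that all centres use one clock.

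The conclusion goes no further. The text does not establish a difference in follow-up between the arms, a direction of error for every abstinence definition, or any effect on the sample size.

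**What to change.** In the Follow-up period section, replace the time origin of visit 3 so that it is scheduled at 12 months after the intervention visit (visit 1), with one visit window that is the same in both arms. This brings visit 3 into line with visit 2 and with the Objectives, Main outcome variables and Analysis strategy sections, none of which then needs to change.

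A single clock from randomisation would also be defensible under intention to treat, but it would mean rewriting those three sections and the timing of visit 2.

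The cost is one sentence in the visit schedule and a last visit that moves later by about L. The change should be made before final visits are booked.
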